### Assignment of interventions

#### Randomization

Random allocation is stratified by center [45]. Patients are assigned to intervention or control group in the study after the eligibility criteria are met. The randomization is performed by following a list of random allocation generated by computer, by the project manager. The unit of randomization is then the patient since the enrollment in the study begins with the patient. However, to limit the risk of contamination due to the fact that a RP can have several patients included in the study, patients with the same RP will be allocated to the same study group. Specifically, each patient coming in geriatric or memory consultation and whose the RP was not identified for a patient previously included, will be assigned randomly to one of the study groups: intervention, or control. Patient will be enrolled by the geriatric/neurologist doctor during the consultation. When a new patient has the same RP that a patient previously enrolled in the study, this new patient will automatically be assigned to the same study group as the previous patient. Finally, the number of patients per RP will be limited to 4.

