#### Descriptive analyzes

A flow-chart will be presented to describe the number of RP per study group, the number of patients selected at inclusion, and the number of patients being followed according to the terms of the protocol, and the loss of follow-up.

Patient characteristics will be compared between the participating centers. Patient characteristics will be compared between the included and followed patients in the study and patients loss of follow-up to assess possible bias. Patient characteristics at baseline will be described for the entire study population, and study group. Quantitative variables will be summarized by mean and standard deviation or median and percentiles if their distribution is not symmetrical. Categorical variables will be presented by frequencies and numbers.Comparisons will be made to test patient characteristics at baseline between the two allocation groups. Means will be compared using the Student *t* test or Mann-Whitney U as appropriate. The proportions will be compared using the chi-square test of two Pearson. The tests will be adjusted to the design effect of the study [49, 50].

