#### Comparative analyzes to assess the impact of the intervention on the primary outcome

The ICC will be calculated on the primary outcome for the entire population and by groups to verify that the correlation between observations is similar between groups. The effect of the intervention on evolution of the level of autonomy function will be estimated in a generalized linear mixed model. The mixed model will account for both fixed and random effects, hierarchy data (patient characteristics correlated between them for a same RP) and repeated measurements of the primary outcome [51, 52]. The evolution of the primary outcome will be defined as the dependent variable, explained by the effect of the study group, the time effect and the interaction between these two effects. The intervention will be considered significant if the interaction between time and the study group is significant. The significance level of each term in the model will be presented. The coefficients associated with variables in the model, their 95% confidence interval and significance level will be presented. The effects of covariates will be tested in the model: recruiting center, age, sex, comorbidities, education level and estimates will be adjusted if the effects are significant to account for these confounders. The interaction between patient characteristics and study group will be tested one by one, and analyzes will be stratified if the interactions are significant and that the result is considered clinically relevant.

The impact of the intervention on the secondary outcomes will be investigated using generalized linear mixed models. To explain the dependent variables, other models such as nonlinear mixed effects models or Cox model will be used [53].

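### Covariates in the primary model, including the stratification factor center, are kept only if significant, and effect modification is tested as characteristic-by-group although the effect is defined as group-by-time

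*Protocol article*

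**What the plan says.** The section on comparative analyzes of the primary outcome describes a mixed model whose dependent variable is "explained by the effect of the study group, the time effect and the interaction between these two effects". The decision rule follows: "The intervention will be considered significant if the interaction between time and the study group is significant".

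The same section then makes adjustment conditional, in that "estimates will be adjusted if the effects are significant to account for these confounders". The covariates put to this test are named just before that rule: "The effects of covariates will be tested in the model: recruiting center, age, sex, comorbidities, education level". The Randomization section says: "Random allocation is stratified by center". Center is therefore both the stratification factor and one of the covariates that must pass a test to stay in.

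On effect modification the plan says: "The interaction between patient characteristics and study group will be tested one by one, and analyzes will be stratified if the interactions are significant". The sentence goes on to require that the result also be judged clinically relevant. Time is not named in this interaction.

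The general Statistical analysis section sets a two-sided 0.05 level for the primary outcome. Its remark on adjusting the threshold refers to sub-analyses of secondary outcomes and applies only where appropriate.

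**The concern.** There are two separate problems, and both lie in what the plan states rather than in detail it leaves out.

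**Covariate rule.** In a randomized trial, covariates belong in the model because they are prognostic and named in advance, or because the allocation used them. Passing a significance test is not the reason. Under the stated rule, a design factor can be dropped because of its p-value. The adjusted set is known only after the data are seen, and it may differ between the IADL and DAD-6 analyses, since each scale is analyzed separately.

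**Effect-modification rule.** Success is defined by the group-by-time term. A characteristic modifies that effect through characteristic-by-group-by-time. A characteristic-by-group term without time asks whether the average group difference varies with the characteristic, which is a different question. The tests are run one at a time on characteristics that the article does not list, and a significant result can lead to a stratified analysis. What is at stake is subgroup findings that arise by chance, or real modification of the 18-month change that is missed.

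**Working it through.** The plan gives no figure of its own on this point, so there is none to reproduce.

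**1. Where the data can choose.** Group, time, group-by-time, the hierarchical structure and the decision rule are all fixed. Five named covariates are optional, so the number of possible adjusted sets per scale is 2^5 = 32. This counts the freedom in the rule; it does not measure bias.

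**2. Does the covariate rule disturb the group-by-time test?** A null simulation was run with 302 patients, visits at 0, 1, 6 and 18 months, about 25% missing at month 18, a random patient intercept and 2000 runs per scenario. The covariate effects and variances are assumptions, since the article gives none.

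| Group-by-time, no true effect | Unadjusted | Keep if significant | Always adjusted |
|---|---|---|---|
| Type I error, covariates affect level only | 4.65% | 4.70% | 4.60% |
| Type I error, age-like covariate also affects slope | 5.75% | 5.60% | 5.55% |

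The simulation error of each rate is about √(0.05 × 0.95 / 2000) = 0.5 percentage points, so the rules cannot be told apart. The mean shift in the coefficient between the unadjusted and selected models was about 0.01, against a standard error of 0.23. Center, given a true effect by assumption, was kept in only 74% and 73% of runs, so dropping it is a realistic outcome.

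The simulation has limits. The link was the identity, dropout did not depend on covariates, physician clustering was left out, and allocation was 1:1 without stratification. A non-identity link or covariate-dependent dropout could make the rule matter more.

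**3. Chance of a false significant interaction.** For k independent tests at 0.05 the chance is 1 − 0.95^k.

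- k = 4 (age, sex, comorbidities, education): 1 − 0.95^4 = 1 − 0.8145 = 18.5%.
- k = 5 (center added): 1 − 0.95^5 = 1 − 0.7738 = 22.6%.

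The values of k are assumptions taken from the covariate list, because the article does not list the characteristics for interaction tests. The 0.05 level per interaction test is also assumed. Clinical relevance is required as well, so both figures are upper bounds on the chance of a false split.

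**4. What the two-way term measures.** Suppose a characteristic modifies the intervention effect by an amount that grows linearly from 0 at baseline to D at month 18. A term without time picks up roughly the average over visits, here with equal weights.

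- Month 0 counted as a response: (0 + 1/18 + 6/18 + 1)/4 × D = 0.347 D.
- Month 0 not a response: (1/18 + 6/18 + 1)/3 × D = 0.463 D.

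Both figures rest on the linear-growth and equal-weight assumptions. They show the direction of the mismatch and are not estimates of lost power.

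**The case against.** The strongest reply is that little is left to the data. The core terms and the decision rule are set in advance, and so is the pool of candidate covariates. Time-constant main effects hardly touch a group-by-time contrast, which is largely a within-patient comparison, and the simulation agrees. This stands. A reader might infer that the whole primary model is chosen by the data, or that its p-value is materially inflated; neither the text nor the check supports that.

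Other stronger readings also fail:

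- **That stratified results replace the overall result.** The article says only that analyses will be stratified, and its success criterion is the overall interaction.
- **That there is a 23% chance of a false split.** This ignores the clinical-relevance condition and assumes five tests.
- **That the two-way test sees only 35% of the modification.** This holds only if month 0 is a response.
- **That baseline tests feed into model selection.** The Descriptive analyzes section says "Comparisons will be made to test patient characteristics at baseline between the two allocation groups", but nothing links those tests to the choice of covariates.

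It can also be said that the article names the evolution of the outcome as the dependent variable. If that means change from baseline, a characteristic-by-group term already concerns modification of change. This is a fair alternative reading, and it is why the second problem is stated conditionally. The trial also describes its framework as exploratory, which softens the multiplicity point but does not bring the interaction test into line with the defined effect.

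A separate analysis plan might settle these points. To do so it would have to overrule a stated rule, not merely add detail.

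**Conclusion.** The concern holds in a limited form. The plan lets the stratification factor and four other named covariates enter the primary model only on significance, which departs from the design and makes the adjusted set depend on the data. The numerical effect on the group-by-time test is probably small: 4.7% against 4.6% type I error, and a shift of about 0.01 against a standard error of 0.23. That conclusion rests on a linear model, assumed covariate effects and dropout unrelated to covariates.

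The effect-modification rule is aimed at a different quantity from the one that defines success, provided the repeated scores are the response. The chance of at least one false significant interaction is about 18.5% to 22.6% with four to five independent tests at 0.05, and the chance of a false split is lower. The change is worth making because it is specific and nearly free, not because large harm to the main test has been shown.

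**What to change.** - Always include center in the primary model. Include age, sex, comorbidities and education level in a form fixed in advance, whatever their p-values. Add the baseline score as a covariate only if month 0 is not also a response, since it should not serve as both.
- State that the overall group-by-time effect from this model remains the primary result, whatever the interaction tests show.
- Replace the one-by-one characteristic-by-group tests with characteristic-by-group-by-time terms for a short list named in advance, and label them exploratory.

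The cost is wording and a few degrees of freedom. Center uses one, as there are two centers, and about 302 × 0.75 = 226 patients are expected at month 18. The analysis already calls for all of these covariates, so no new data are needed.

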### Participant timeline

The OPTIM study is part of the routine care of patients at geriatric/memory center. Four successive evaluations are planned for the participants (Table 1). The inclusion is planned at the first consultation of the patients at the geriatric/memory center. Three others evaluations during follow-up are planned: at 1 month and after 6 months and 18 months. At 6 and 18 months, the patients will undergo a consultation at the geriatric/memory center, whereas the limited evaluation at 1 month will be performed by phone with the primary caregiver.

**Table 1 Tab1:** Schedule of enrolment, intervention and assessments of the OPTIM study

	Study Period				
	Enrolment	Allocation	Follow-up		
Timepoint	- *t1*	0	*t* _*1*_ *: 1 month*	*t* _*2*_: *6 months*	*t* _*3*_: *18 months - Close-out*
Enrolment:					
Eligibility screen	X				
Information to patients/careviger	X				
Collection of non-opposition to participate	X				
Randomized allocation		X			
Intervention:					
*(1) Intervention: Optimization of drug prescribing*		X	X	X	
*(2) Control*					
Assessments:					
*Collected in patient record:* * Sociodemographic data * Diagnosis and stage * Current comorbidities, history of comorbidities, lifestyle habits * Biological exam and artrial pressure when available		X			
*Primary outcomes:* * IADL scale * DAD-6 scale		X	X	X	X
*Secondary outcomes:* * MMSE (cognitive function) * mini-GDS (depression) * Hamilton scale (anxiety) * Pain scale * EUROQOL-5D (quality of life) * Girerd scale (compliance to drug prescribing) * Event and date of event: hospitalization, falls, recourse of emergency, institutionalization, death		X		X	X
Drugs prescribing		X	X	X	X

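### Success rests on group-by-time, but no covariate-by-time term is named, so on the natural reading the promised covariate adjustment hardly reaches the tested effect

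*Protocol article*

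**What the plan says.** All of the relevant text is in the protocol article, under the heading on comparative analyses of the primary outcome.

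- **Model:** the effect "will be estimated in a generalized linear mixed model". No link or distribution is given.
- **Dependent variable:** "The evolution of the primary outcome will be defined as the dependent variable". This leaves open whether the repeated score or its change is modelled.
- **Core terms:** the outcome is "explained by the effect of the study group, the time effect and the interaction between these two effects".
- **Decision rule:** "The intervention will be considered significant if the interaction between time and the study group is significant".
- **Covariates:** "The effects of covariates will be tested in the model: recruiting center, age, sex, comorbidities, education level", followed by the statement that "estimates will be adjusted if the effects are significant to account for these confounders".
- **Covariate interactions:** the only kind named is with study group: "The interaction between patient characteristics and study group will be tested one by one".

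The section on the participant timeline adds the visits: "Three others evaluations during follow-up are planned: at 1 month and after 6 months and 18 months", after the assessment at inclusion.

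**The concern.** The five listed covariates are fixed for each patient, or are treated as fixed at baseline. A main effect of such a covariate moves a patient's score by the same amount at every visit. The group-by-time term compares how scores change between visits, and a constant shift does not enter that comparison. A significant covariate would therefore be added to the model, the result would be called adjusted, and the coefficient that decides the trial would stay where it was.

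This matters because the covariates plausibly affect the rate of decline as well as the level. The Background itself lists several diseases and cognitive impairment as influences on loss of autonomy. Randomization is stratified by center only, and later patients of an already enrolled referring physician follow that physician's group, so age and comorbidity are not balanced by design. If one arm happens to be older and declines faster, the listed terms would not remove that difference from the tested effect.

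**Working it through.** **Inputs from the protocol article (sample size and timeline sections).** Control change 1.3 points, SD 2; intervention change 1.04; visits at 0, 1, 6 and 18 months; 232 patients before the attrition allowance, so 232 / 2 = 116 per arm; 25% attrition; 302 in total. The target difference reproduces: 0.20 × 1.3 = 0.26, and 1.3 − 0.26 = 1.04.

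**Assumptions, not in the article.** Covariate-to-change correlation r of 0.3 to 0.4; the variance components, age effects and age imbalance used in the simulations.

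**1. Algebra, identity link.** For patient i in group G with baseline covariate X:

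Y(i,t) = b0 + b1·G + b2·t + b3·G·t + c·X + u(i) + v(i)·t + e(i,t)

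Subtracting the baseline score gives

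Y(i,t) − Y(i,0) = b2·t + b3·G·t + v(i)·t + e(i,t) − e(i,0).

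The term c·X has gone, so it cannot adjust b3. A covariate-by-group term, d·X·G, is also constant over time and drops out in the same way. A term k·X·t does not drop out. If the change is itself the dependent variable, a covariate main effect adjusts the group main effect, but still not the interaction that is tested.

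**2. Simulation, 302 patients, covariance held at its known value.** True 18-month difference −0.26; age assumed to add 0.004 points per year of age per month; one arm 2 years older with an age SD of 7, an imbalance of 2 / 7 = 0.29 SD chosen to make the mechanism visible. The expected distortion is 0.004 × 2 × 18 = 0.144. Mean of 60 runs:

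| Data | No covariates | Main effects | Covariate × time |
|---|---|---|---|
| Complete | −0.085 (SE 0.170) | −0.085 (SE 0.170) | −0.222 (SE 0.172) |
| About 25% attrition related to age | −0.091 (SE 0.196) | −0.091 (SE 0.196) | −0.224 (SE 0.198) |

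With complete data, the first two columns differ in any run by no more than 2 × 10⁻¹⁵. With attrition they differ by 0.004 on average and 0.012 at most. When the variances were estimated by REML in six complete data sets without imbalance, the estimates again agreed and the mean SEs were 1.387 and 1.388, a difference of about 0.1%. (That run assumed different variances, so only the comparison is informative.)

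**3. Second simulation, 116 per arm, change SD 2.** With complete data, the estimates with and without the main effect agreed to four decimals, with SE 0.254 in both. With 25% missing at 18 months, the largest difference was 0.02 to 0.06.

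**4. Size of a chance imbalance.** One standard error of the covariate difference is √(2/116) = 0.131 SD. The shift in the effect is imbalance × r × SD of change:

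- r = 0.3: 0.131 × 0.3 × 2 = 0.079
- r = 0.4: 0.131 × 0.4 × 2 = 0.105

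That is about 0.08 to 0.10 points, or 30% to 40% of 0.26.

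**5. Precision.** With covariate-by-time terms, the SE of 0.254 in step 3 fell to 0.243 (r = 0.3) or 0.233 (r = 0.4), which is 4.3% or 8.3% lower. There is no such gain in step 2, because the model variance was held fixed there.

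**6. Non-identity link.** In four logit fits with complete data, adding the covariate main effect moved the interaction by about 2% to 15% (for example −0.309 to −0.355). In those data the covariate had no effect on the rate of change, so this movement does not show that a main effect would remove an imbalance in decline.

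**The case against.** The strongest reply is that main-effects-only entry is inferred. The article says that covariate effects will be tested in the model; it does not exclude covariate-by-time terms, and a fuller document may specify them. This stands, and the point is conditional for that reason. The article does, however, spell out group-by-time and covariate-by-group interactions, and it gives confounder control as the purpose of the adjustment. A reader who follows it as written would fit main effects.

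A reader might infer that the covariates cannot change the tested effect at all. The documents do not support that. The model is called generalized, the link is not named, both scales are bounded, and 25% attrition is expected. Exact invariance needs an identity link and complete data. Under attrition the largest shift found was 0.06 points, which is 0.06 / 0.26 = 23% of the target, although the average in the other simulation was only 0.004. The sample size section does express the effect as a mean change in points with an SD, which favours a linear scale.

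A reader might also infer that the primary test is biased. It is not. Randomization keeps the unadjusted contrast valid on average, and chance imbalance is already reflected in its standard error. Shifts of 60% to 80% of the target arise only at the 95% limit of imbalance, 1.96 × 0.131 = 0.257 SD, combined with the assumed correlation; that is an extreme case.

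Finally, the article promises to present the model coefficients, so a careful reader could see which terms were fitted. That limits the risk of misreading but does not make the adjustment effective.

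**Conclusion.** The point holds in conditional form. The stated adjustment does not match the stated test: on the natural reading (main effects, linear scale), adjusting for the five covariates leaves group-by-time unchanged with complete data and nearly unchanged at the planned attrition. Nothing else listed in that section fills the gap.

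The consequence is moderate. The unadjusted test is not invalidated. What is forgone is protection against a chance imbalance, typically worth about 0.08 to 0.10 IADL points, and a reduction in standard error of between 4% and 9%. Both figures rest on the assumed correlation of 0.3 to 0.4, for which the article gives no value. An amendment is worthwhile because it is cheap and because a result labelled as adjusted should be adjusted. The point concerns what a covariate does once it is in the model, not the rule for selecting covariates.

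**What to change.** In the section on comparative analyses of the primary outcome, state that each covariate used for adjustment enters together with its interaction with time. Report the group-by-time contrast from that model as the adjusted result. A model of the follow-up scores should be offered as an alternative only if it includes the baseline score.

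The cost is one extra parameter per covariate degree of freedom if time is linear, and three if the four visits are categorical. For five covariates the categorical form needs at least 5 × 3 = 15 parameters, and more if comorbidity or education has several levels. No new data are needed.

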#### Data monitoring

The CRA will ensure the successful completion of the study, and the collection of data. The CRA will also ensure the compliance with the study protocol, and the organization of the follow-up of the patients.

